#### Survey

The study is a case–control study (1000 cases, 1000 controls). The study will have 90% power at a 5% significance level to detect an OR for being a case of 1.146 per SD increase in a continuous predictor variable; for a binary predictor with 50% prevalence, the study will have 90% power to detect an OR for being a case of 1.345; for a binary predictor with a prevalence of 10%, the study will have 90% power to detect an OR for being a case of 1.662.

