##### Recruitment

At least 3 months after the screening invitation, a subsample of trial participants will be identified from all eight groups, including people who returned (case) and did not return (control) their FIT, and people living in 40% most and least deprived neighbourhoods (based on Scottish Index of Multiple Deprivation (SIMD) quintiles).^34^ The subsample will be sent a postal invitation to complete and return a survey. The aim is to obtain responses from approximately 1000 cases and 1000 controls across the eight groups. Based on previous work, we anticipate achieving a higher response rate from those returning the FIT and a lower response from those not returning the FIT, therefore approximately 11 872 questionnaires will be mailed, as shown in figure 1.^32^ A reminder questionnaire will be sent to those who have not returned the questionnaire after 3 weeks.

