### Sample size

This 2×4 factorial RCT involves the assessment of two interventions, so each will be assessed at a significance level of 2.5%, to preserve an overall Type I error rate of 5%.

The assessment of the effect of the planning tool will involve the comparison of two groups of 20 000 participants. At a significance level of 2.5%, this gives 90% power to detect an increase in uptake rates from 65% to 66.8%. Alternatively, if the intervention increases uptake rates from 65% to 68%, the 97.5% CI for the difference in uptake rates will have a width of±1.06%.

The assessment of the effect of suggested deadlines for FIT kit return will involve four groups of 10 000 participants. Comparing each suggested deadline with the control group (no deadline) at a significance level of 0.83% (one-third of 2.5%), there will be 90% power to detect increases in uptake rates from 65% to 67.63%. If an intervention increases uptake from 65% to 68%, the 99.17% CI for the difference in uptake rates will have a width of±1.76%.

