##### Survey analysis

Descriptive statistics, χ^2^ tests, analysis of variance and logistic regression will be used to examine cognitive and behavioural mechanism differences between the intervention and control groups and their association with FIT kit return.

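### The survey's 90% power for an OR of 1.146 per SD is overstated: 1000 cases and 1000 controls give about 86%, and the OR detectable with 90% power is 1.156

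*Protocol article*

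**What the plan says.** The Survey paragraph under Sample size fixes the design: "The study is a case–control study (1000 cases, 1000 controls"). The Recruitment text for the questionnaire survey gives the same target: "The aim is to obtain responses from approximately 1000 cases and 1000 controls across the eight groups".

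The Survey paragraph then lists three detectable effects:

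- Continuous predictor: "The study will have 90% power at a 5% significance level to detect an OR for being a case of 1.146 per SD increase".
- Common binary predictor: "for a binary predictor with 50% prevalence, the study will have 90% power to detect an OR for being a case of 1.345".
- Uncommon binary predictor: "for a binary predictor with a prevalence of 10%, the study will have 90% power to detect an OR for being a case of 1.662".

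The paragraph names no formula, sidedness, covariate adjustment or variance inflation. The Survey analysis section lists logistic regression among its methods: "logistic regression will be used to examine cognitive and behavioural mechanism differences between the intervention and control groups and their association with FIT kit return".

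**The concern.** The paragraph gives everything needed to recompute the continuous-predictor figure except sidedness, and the recomputed OR is larger than the printed one. The two binary figures err slightly on the cautious side, whereas this one errs on the favourable side.

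The survey addresses the research question on cognitive and behavioural mechanisms, which the Outcomes section lists as a secondary outcome. The questionnaire includes action and coping planning items. If these are analysed as scale scores, the continuous-predictor figure is the one that describes the survey's sensitivity. That use is an inference, because the paragraph refers only to a continuous predictor in general. A reader who relies on the figure would take the chance of missing an OR of 1.146 per SD to be 10% when it is about 14%.

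**Working it through.** **Inputs, all from the Survey paragraph under Sample size.** N = 2000, with half of them cases (p = 0.5); significance level 5%; power 90%; OR 1.146 per SD, so ln(1.146) = 0.1363. Two-sided testing is assumed (see step 5).

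**1. Power at the stated OR.** For logistic regression on one standardised, normally distributed covariate (Hsieh's formula):

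power = Φ( ln(OR) × √(N·p·(1−p)) − z₀.₉₇₅ )

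√(2000 × 0.5 × 0.5) = √500 = 22.361

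0.1363 × 22.361 = 3.047; 3.047 − 1.960 = 1.087; Φ(1.087) = **86.2%**, against the stated 90%.

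**2. OR detectable with 90% power.** ln(OR) = (1.960 + 1.282)/22.361 = 3.2415/22.361 = 0.1450, so OR = **1.156**. The same formula at 86% power gives 1.1456, which rounds to the printed 1.146.

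**3. Sample size for 90% power at 1.146.** N = (1.960 + 1.282)² / (0.25 × 0.1363²) = 2263, or **2,264** for equal groups (1132 in each). That is 264 more than 2000, or 13%.

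**4. Other methods with the same inputs.**

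| Method | Power at 1.146 | OR for 90% power |
|---|---|---|
| Hsieh formula / two means | 86.2% | 1.1560 |
| Noncentral t | 86.1% | 1.1561 |
| Hsieh 1989 formula | – | 1.1568 |
| Simulated Wald logistic test, 4,000 runs | 86.0% | 90.0% power at 1.156 |
| Separate simulation, 20,000 runs | 86.4% | 90.0% power at 1.156 |

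**5. Could a different reading give 1.146?**

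- *One-sided 5% test.* Power at 1.146 is 92.0%, the 90%-power OR is 1.140, and the N needed at 1.146 is 1845. This does not give 1.146 with 2000 responses.
- *Sidedness elsewhere.* The deadline comparison under Sample size says "there will be 90% power to detect increases in uptake rates from 65% to 67.63"%. With 10 000 per group and a significance level of 0.83%, that is 90.3% power two-sided and 93.8% one-sided, so it fits a two-sided test.
- *Unequal split.* With 65% cases the Hsieh 1989 formula gives 1.147, but the article states 1000 and 1000. The formula in step 1 with 65% cases gives 1.164, because p(1−p) is largest at p = 0.5.
- *Covariate adjustment.* None is stated, and variance inflation would lower the power further.

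**6. The companion binary figures.** The step 1 formula, with the predictor's variance added, is power = Φ( ln(OR) × √(500 × π(1−π)) − 1.960 ), where π is the overall prevalence.

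- π = 0.5, OR 1.345: 0.2964 × √125 = 3.314; Φ(1.354) = 91.2%.
- π = 0.1, OR 1.662: 0.5080 × √45 = 3.408; Φ(1.448) = 92.6%.

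Comparing two proportions directly gives 91.2% and 91.9%. With continuity correction, 986 and 976 per group are needed for 90% power, both just under 1000. One-sided, the two figures would have 95.2% and 95.7% power. The binary ORs therefore fit a two-sided 5% test with a small margin, and only the continuous figure falls short.

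**The case against.** The strongest objection concerns weight, not arithmetic. The survey serves secondary outcomes, and the power of the primary trial comparisons is unaffected. The gap is 0.010 on the OR scale and about 4 percentage points of power. The paragraph starts from 1000 and 1000 and reports what can be detected. It does not say that the sample size was derived from 1.146, or that 1.146 is the smallest effect that matters. The response numbers are themselves approximate targets. All of this stands. It limits the consequence but does not make the printed figure correct. For the same reason, the 14% type II error applies to a true OR of exactly 1.146; at 1.156 it is 10%.

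A second objection is that the paragraph states neither method nor sidedness, and that a one-sided test would give at least 90% power at 1.146. It is right that two-sided testing is an assumption for the survey. However, a one-sided test gives a detectable OR of 1.140, and it would put the two companion ORs at about 95% to 96% power instead of 90%. It does not explain the set of three figures.

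Finally, 1.146 may simply be a one-digit slip for 1.156. That is plausible but cannot be shown from the document, and the correction would be the same.

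**Conclusion.** The point holds. With 1000 cases, 1000 controls and a two-sided 5% test, the survey has about 86% power, not 90%, for an OR of 1.146 per SD; the OR detectable with 90% power is 1.156. This rests on two-sided testing and a single standardised, approximately normal predictor without adjustment. No reading tested that keeps the stated 1:1 split gives 1.146 at 90% power. The error is isolated, since the two binary ORs in the same sentence are sound and slightly conservative. Its effect is confined to the secondary mechanism survey.

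**What to change.** Restate the continuous-predictor figure as 90% power to detect an OR of 1.156 per SD, or keep 1.146 and give the power as 86%. Add that the test is two-sided. If 1.146 came from another method or another case fraction, name that method and its inputs so that the figure can be reproduced.

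The cost is one number, a short clause on sidedness and a slightly less favourable stated effect. The survey size, mailing and analysis stay as they are. Keeping 90% power at 1.146 would instead need about 2,264 responses. At the planned ratio of mailings to responses that means 11 872 × 2264/2000 ≈ 13 440 questionnaires, which correcting the text does not require.

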### Trial data collection and management

For the purposes of this study, two additional variables will be added to the Scottish Bowel Screening Programme invitation data file: (1) a unique identifier for each participant; and (2) a variable coding for the allocated condition. The pseudonymised participant data including FIT kit return data will be transferred from the Scottish Bowel Screening Centre in Dundee to the Robertson Centre for Biostatistics at the University of Glasgow using a secure file transfer protocol.

### Data analysis plan

Primary and secondary outcome measures will be summarised using descriptive statistics.

#### Primary outcome

The primary analysis will use a logistic regression model, including a binary variable for whether the planning tool was provided, and a four-level categorical variable denoting which deadline was suggested. Age, sex and area deprivation (measured by the SIMD^34^) will be included in the model, to improve model specification. The main effects of each intervention will be reported as an OR, with a CI and p-value. For the estimate of the effect of the planning tool, a 97.5% CI will be reported. For estimates of the effect of alternative suggested deadlines, relative to no deadline, 99.17% CIs will be used. Subsequent analyses will model the interaction between the two interventions, to assess whether the interventions have independent effects or are synergistic. We shall also model interactions between each intervention effect and age, sex and deprivation, to assess whether the interventions have different effects for subgroups of the population. Assessing uptake by deprivation is important given the disparities in screening uptake by deprivation (53% most deprived vs 73% least deprived);^7^ which any intervention could reduce or exacerbate.^36^

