### Theoretical rationale

CRC screening uptake remains suboptimal, despite high levels of public enthusiasm. In a Scottish survey, 85% of people reported intending to complete the FIT,^9^ yet participation is 65%.^7^ This suggests that apparent enthusiasm for the new FIT is not being translated into uptake. A major reason for this disparity may be that people are ‘not getting round to it’,^10^ reflecting the well-recognised intention-behaviour gap and consistent with the observation that much of our behaviour is determined by factors other than conscious, deliberative control.^11–14^ This disparity is consistent with previous work on ‘inclined abstainers’,^13^ showing that a proportion of people are inclined to participate in screening but fail to do it. This explanation seems particularly likely for CRC screening which, unusually for a screening test, is self-completed at home. General open-ended intentions to act often fail to lead to the desired behaviour.^15^ Our previous research has found that people often put off or forget to complete and return the FIT.^16^ Additional support through prompting the setting of FIT completion goals and planning may better support participation among those inclined to complete the FIT but who might otherwise fail to act.

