### Study setting

This is a single-centre trial to be conducted in collaboration with the Scottish Bowel Screening Centre based in Dundee, Scotland, and integrated into the national CRC screening programme. In Scotland, colorectal screening is offered to people aged 50–74, every 2 years, by single-sample FIT.

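### The primary model adjusts only for age, sex and SIMD; return at the previous invitation, probably obtainable in a two-yearly programme, would add power at little cost

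*Protocol article*

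**What the plan says.** Under Data analysis plan, Primary outcome: "The primary analysis will use a logistic regression model, including a binary variable for whether the planning tool was provided" and a four-level deadline variable. The covariates are age, sex and deprivation by SIMD, which "will be included in the model, to improve model specification". Results are reported on the odds ratio scale: "The main effects of each intervention will be reported as an OR, with a CI and p-value". Interactions are planned between the two interventions, and between each intervention and age, sex and deprivation. Screening history is not mentioned as a covariate, a subgroup factor or a transferred variable.

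Three other sections bear on what could be used:

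- Study setting: screening is offered to people aged 50–74, "every 2 years, by single-sample FIT".
- Trial data collection and management: "two additional variables will be added to the Scottish Bowel Screening Programme invitation data file" (an identifier and the allocation), and the screening centre transfers pseudonymised data, including kit return, to the analysing unit.
- Theoretical rationale: the interventions are aimed at a group described by the observation that "a proportion of people are inclined to participate in screening but fail to do it".

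**The concern.** The primary outcome is return of a correctly completed kit within 3 months. In a programme that invites the same people every two years, most of a consecutive sample of invitees should have an earlier invitation with a recorded result. Whether that kit came back is the natural baseline measure of the outcome and is likely to predict it well.

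The only listed covariate for which the article gives a gradient is deprivation, at 53% versus 73% uptake, and that gradient explains little of the outcome (see the working). The trial looks for differences of roughly 2 to 3 percentage points. Research question 4 also compares deadline lengths with one another, where differences may be smaller still and for which the Sample size section gives no power. Unused prognostic information costs most for effects of that size.

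The planned subgroup factors also include no marker of past screening behaviour, although the rationale is about people who intend to screen and do not act.

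**Working it through.** **1. The plan's own figures.** Inputs from Sample size: 65% control uptake; tool 20,000 v 20,000 at α = 2.5% (z = 2.241); each deadline 10,000 v 10,000 at α = 0.83% (z = 2.638); all tests two-sided.

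- Deadline, 65% v 67.63%: SE = √[(0.65×0.35 + 0.6763×0.3237)/10,000] = 0.00668. Then 0.0263/0.00668 = 3.94, and power = Φ(3.94 − 2.638) = 90%. This reproduces.
- CI half-widths at 65% v 68%: 1.06 points (tool) and 1.76 points (deadline). Both reproduce.
- Tool, 65% v 66.8%: SE = 0.00474, 0.018/0.00474 = 3.80, and power = Φ(3.80 − 2.241) = 94%. The stated 90% is therefore conservative, which is a separate matter. The difference that gives 90% power is about (2.241 + 1.282) × √(2×0.65×0.35/20,000) = 1.68 points, and that is used for the tool below.

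**2. What deprivation explains.** Assume equal quintiles, linear from 53% to 73%. The between-quintile variance is 0.0050 and the total is 0.63×0.37 = 0.2331, so R² is about 2%.

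**3. What prior return might explain (assumed; the article has no figures).** R² = Σ w(p − p̄)² / [p̄(1 − p̄)] over prior returners / invited non-returners / not previously invited.

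| Scenario | Shares (%) | Current return (%) | p̄ | R² | Equivalent extra sample, 1/(1 − R²) − 1 |
|---|---|---|---|---|---|
| A | 55/30/15 | 75/50/62 | 0.656 | 0.055 | 6% |
| B | 55/35/10 | 85/35/52 | 0.642 | 0.240 | 32% |
| C | 58/32/10 | 90/22/50 | 0.642 | 0.425 | 74% |

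Example, A: 0.55×0.0945² + 0.30×0.1555² + 0.15×0.0355² = 0.0124, and 0.0124/0.2258 = 0.055.

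**4. Effect on the risk difference.** The SE is multiplied by √(1 − R²) = 0.972 / 0.872 / 0.758.

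| | Unadjusted | A | B | C |
|---|---|---|---|---|
| Tool power at 1.68 points | 90% | 92% | 97% | 99% |
| Deadline power at 2.63 points | 90% | 92% | 97% | 99% |
| Tool CI half-width (points) | 1.06 | 1.03 | 0.92 | 0.80 |
| Deadline CI half-width (points) | 1.76 | 1.71 | 1.53 | 1.33 |

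**5. Effect on the planned odds ratio.** In each stratum the control return is p₀ and the treated return is expit(logit p₀ + b), with b chosen to give the same overall rise. SE(b) = 1/√[n Σ w v₀v₁/(v₀ + v₁)], where v = p(1 − p).

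| Deadline comparison | Unadjusted | A | B | C |
|---|---|---|---|---|
| OR | 1.12–1.13 | 1.13 | 1.16 | 1.22 |
| SE of log OR | 0.030 | 0.031 | 0.034 | 0.039 |
| Power | 90–91% | 92% | 97% | 99% |

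The SE rises by 3%, 14% and 31%. The conditional log OR rises by more, so power goes up while the interval for the log OR gets wider.

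**6. A different set of assumptions.** With 65% prior returners, return of 75/46% up to 90/19% and no other covariates, R² runs from 8% to 51%. Deadline power goes from 90.3% to between 92.8% and 99.8%. With 15% lacking history (80/38/63%) it is 94.7%. The direction is the same throughout; the size depends on the assumption. These calculations leave out age, sex and SIMD, and overlap with them would lower the gains somewhat.

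**The case against.** **Nothing in the planned analysis is invalid.** This stands. Allocation is by permuted blocks of eight, the sample size uses unadjusted proportions and claims nothing from covariates, and the planned 90% is met. A reader might infer bias or an underpowered trial from the omission; the article supports neither.

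**The field may not be available.** This also stands. A reader might infer from two-yearly recall that the transferred file already holds previous-round return. The article gives the interval and says that return data are transferred, but it does not list the file's contents or mention history. First-time invitees would have none in any case.

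**Adjustment does not sharpen the reported measure.** This is correct. It is tempting to say that the intervals for the deadline odds ratios would narrow, but step 5 shows the opposite. The shift in the OR is not always slight: in scenario C it goes from 1.12 to 1.22.

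**Prior non-return is not the target group.** This stands in part. Inclined abstainers are defined by intention, and prior non-returners also include people who do not intend to screen. It is an imperfect marker, though closer to the behaviour than age, sex or SIMD. The survey covers mechanisms, but only in a subsample.

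**The analysis plan may add covariates.** It may. But the article already names the covariates of the primary model, so this comments on a stated choice and does not allege a gap.

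**Conclusion.** The point holds as a missed gain in efficiency. The stated covariate list leaves out the baseline version of the primary outcome, which the programme can probably supply.

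Under the assumed associations, power at 1.68 points (tool) and 2.63 points (each deadline) rises from about 90% to 92–99%. At the low end the gain is small: at the protocol's 1.8 points the tool goes from about 94% to 95%. Only the direction is secure. The size rests on assumed return rates by prior status, and the whole point depends on the field being available.

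**What to change.** 1. Ask the screening centre whether status at the previous invitation can be extracted for all randomised people.
2. If so, prespecify it before unblinding as a three-level covariate in the primary logistic model (returned / invited but not returned / not previously invited), beside age, sex and SIMD.
3. Add its interaction with each intervention to the listed subgroup analyses, described as a marker of past behaviour and not of intention.
4. Report a model-standardised risk difference with its CI, at the same 97.5% and 99.17% levels, beside the conditional OR.

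Costs: one more pseudonymised field, one model term and one further interaction per intervention. Trial participants give no individual consent and protocol amendments go to the sponsor and the ethics committee, so the field may need a data-permission or protocol amendment. The conditional OR will lie further from 1 with a larger SE on the log scale, so the report should say that it is not directly comparable with an unadjusted OR. If the field cannot be had, the planned model stands.

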##### Survey analysis

Descriptive statistics, χ^2^ tests, analysis of variance and logistic regression will be used to examine cognitive and behavioural mechanism differences between the intervention and control groups and their association with FIT kit return.

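### The survey is sampled on FIT return and deprivation, but the methods named for mechanism and acceptability levels and for between-arm comparisons take no account of that sampling

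*Protocol article*

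**What the plan says.** Under Questionnaire survey, Recruitment, the protocol article draws the survey from all eight trial groups, "including people who returned (case) and did not return (control) their FIT", and "people living in 40% most and least deprived neighbourhoods". The middle deprivation quintile is not named. The target is an overall one: "The aim is to obtain responses from approximately 1000 cases and 1000 controls across the eight groups". The text refers to figure 1 for the mailing of 11 872 questionnaires; that figure is not available here.

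Under Sample size, Survey, the power statements all concern the odds ratio for being a case, that is, for having returned the FIT.

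Under Survey analysis, one sentence names logistic regression, ANOVA, chi-squared tests and descriptive summaries. It gives them two purposes. The first is that they "will be used to examine cognitive and behavioural mechanism differences between the intervention and control groups". The second is the association of mechanisms with return. Outcomes lists mechanisms and acceptability as secondary, and the opening line of the Data analysis plan has secondary outcomes summarised descriptively. Weighting for the sampling is not mentioned in any of these sections.

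**The concern.** Return of the FIT is the trial's primary outcome and is observed after randomisation. Research question 5 supposes a chain in which allocation changes a mechanism and the mechanism changes return. Selecting respondents on return therefore selects on a consequence of both allocation and mechanism. A case-control sample still estimates the odds ratio between mechanism and return correctly. Without adjustment it does not give the level of a mechanism or of acceptability among people invited, and it need not give the arm difference in a mechanism that randomisation would otherwise protect.

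Two things are at stake. Acceptability (research question 6) is meant to inform national implementation, so its level in the invited population matters. And the mechanisms most strongly related to return are the ones whose arm difference would be understated.

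**Working it through.** **The plan's own figure.** With 1000 cases and 1000 controls, two-sided 5%, and 50% prevalence in controls, an odds ratio of 1.345 gives 0.5×1.345/(0.5+0.5×1.345) = 57.4% in cases. A two-proportion test then has 91.0% power against the stated 90%. An odds ratio of 1.662 at 10% overall prevalence gives 91.9%. So the binary figures hold for the purpose they serve. (The continuous figure, 1.146 per SD, gives about 86% two-sided; that is a separate matter.)

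**Inputs.** From the article: 65% uptake (Theoretical rationale), effects of 65% to 66.8% or 68% (Sample size), and a 50:50 survey target. Not in the article, hence assumed: the returner/non-returner gap in a mechanism (0.3 to 1.2 SD) and in acceptability (90%/80% to 90%/40%).

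**Levels.** Population level = 0.65a + 0.35b; unweighted survey level = 0.5a + 0.5b, where a is the level in returners and b in non-returners. The error is −0.15(a − b).

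| Returners / non-returners | Population | Unweighted | Error (points) |
|---|---|---|---|
| 90% / 80% | 86.5% | 85.0% | −1.5 |
| 80% / 50% | 69.5% | 65.0% | −4.5 |
| 90% / 40% | 72.5% | 65.0% | −7.5 |

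For a continuous score the same formula gives 0.15 × gap, or 0.04 to 0.19 SD too low.

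**Arm contrast, binary mechanism.** Suppose an intervention raises a mechanism from 40% to 50%, and return is 80% with it and 55% without.
- Uptake: 0.4×0.80 + 0.6×0.55 = 65.0% in control; 0.5×0.80 + 0.5×0.55 = 67.5% in intervention. This lies within the effects the article considers.
- Mechanism prevalence in control: returners 0.32/0.65 = 49.2%, non-returners 0.08/0.35 = 22.9%.
- Mechanism prevalence in intervention: returners 0.40/0.675 = 59.3%, non-returners 0.10/0.325 = 30.8%.
- *50:50 within each arm:* (59.3 + 30.8)/2 − (49.2 + 22.9)/2 = 45.0 − 36.0 = 9.0 points against a true 10.
- *Fractions depending on return only, common to both arms:* pooled uptake is 66.25%, so returners are sampled in proportion to 0.5/0.6625 = 0.755 and non-returners to 0.5/0.3375 = 1.481. The survey prevalences become 35.7% and 45.4%, a difference of 9.7 points.

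**Arm contrast, continuous mechanism.** Take a standard normal score with logit P(return) linear in the score, uptake 65% against 68%, and 50:50 within each arm.

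| Returner/non-returner gap | True arm difference if the score fully mediates the effect | Unweighted | Attenuation | Spurious difference if the score is unaffected |
|---|---|---|---|---|
| 0.29 SD | 0.458 | 0.449 | 2% | −0.009 |
| 0.84 SD | 0.161 | 0.135 | 16% | −0.026 |
| 1.23 SD | 0.109 | 0.070 | 36% | −0.039 |

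The standard error of an arm difference is √(2/1000) = 0.045 SD for the planning tool and √(2/500) = 0.063 SD for one deadline against none, so the bias is below one standard error throughout. A bias of 0.03 SD would raise a nominal 5% planning-tool comparison to about 10%. At 65% against 66.8% the spurious difference is −0.005 to −0.023 SD. With sampling fractions common to all arms it is only +0.001 to +0.003 SD at 65% against 68%.

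**Cost of weighting.** Restoring 65:35 needs weights 0.65/0.5 = 1.3 and 0.35/0.5 = 0.7. The Kish design effect is 0.5×1.3² + 0.5×0.7² = 1.09, and √1.09 = 1.044.

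**The case against.** The Survey analysis section is one sentence naming families of methods in a condensed article. It does not say the analyses will be unweighted, and weights could be set out in a fuller document. The survey is designed and powered as a case-control study, and its association analysis is sound. The outcomes concerned are secondary. Acceptability is also examined through interviews and helpline calls, and no single pooled percentage is promised; figures reported by return status would be unaffected.

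Much of this stands, and it limits the point. It does not remove it. The article does more than stay silent: it pairs an outcome-selected sample with standard tests for a between-arm purpose that the sample does not directly serve. Nor would the listed logistic regression or ANOVA resolve it by adding return as a covariate. In the binary example the arm difference is 10.0 points among returners and 7.9 among non-returners. Their average is the same 9.0, because adjusting for return conditions on the same post-randomisation outcome.

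Three stronger readings are tempting and are not supported:
- *That the arm effects are biased as a matter of course.* This needs the intervention to change uptake, the mechanism to be related to return, and sampling fractions that differ by arm. The text gives only an overall 1000:1000 target. That 11 872 = 8 × 1484 fits equal mailing per arm, but does not show a fixed case:control ratio in each.
- *That attenuation of about 30% is to be expected.* With return 90% against 45%, the 10 points do read as 7.0 under per-arm 50:50. But uptake then moves from 63% to 67.5%, a gain of 4.5 points against the 3 the article considers at most, and common fractions give 9.5.
- *That sampling on deprivation biases the arm comparison.* Deprivation is fixed before randomisation. Selecting on it affects levels and generalisability, not the randomised contrast itself.

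**Conclusion.** The point holds in a limited form. The methods named do not match the sampling for two uses: describing mechanism and acceptability levels, and comparing mechanisms between arms.

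The error in levels is the firmer part. It needs no intervention effect, only a difference between returners and non-returners, and it runs from 1.5 to 7.5 points over an assumed range. The arm-contrast error is conditional. It is material only with case:control ratios fixed within arms, where it is still at most about 0.04 SD at 65% against 68% uptake, and it is slight if fractions by return are common to all arms. All sizes rest on assumed gaps and on responses close to the 50:50 target. The primary analysis and the association of mechanisms with return are untouched. The change is worth making because it is cheap and the quantities concerned answer research questions 5 and 6.

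**What to change.** Amend the survey analysis wording as follows.

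- For between-arm mechanism comparisons, and for mechanism and acceptability summaries, weight each respondent by the inverse of the sampling-and-response fraction in their cell of arm × return status × SIMD. Collapse sparse cells and use robust standard errors.
- State that inference covers the 40% most and 40% least deprived neighbourhoods.
- Keep the unweighted logistic regression for association with return, adjusted for SIMD as a sampling factor.
- State whether case:control numbers are fixed within each arm or only overall.

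No new data are needed, since allocation, return and SIMD are already held for trial participants. The price is modestly wider intervals: about 4% from restoring 65:35, and more if response varies widely between cells. The weights do not correct for selective response within a cell, and the report should say so.
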